## Abstract

**Background:**

Eye movement desensitization and reprocessing (EMDR) is an evidenced-based treatment for posttraumatic stress disorder (PTSD). Forensic mental health services provide assessment and treatment of people with mental illness and a history of criminal offending, or those who are at risk of offending. Forensic mental health services include high, medium, and low-security inpatient settings as well as prison in-reach and community outpatient services. There is a high prevalence of PTSD in forensic settings and posttraumatic experiences can arise in people who violently offend in the context of serious mental illness (SMI). Successful treatment of PTSD may reduce the risk of relapse and improve clinical outcomes for this population. This study aims to assess the efficacy, risk of harm, and acceptability of EMDR within forensic and rehabilitation mental health services, as compared to treatment as usual (routine care).

**Methods:**

This is a single-blind, randomized controlled trial comparing EMDR therapy to the waiting list (routine care). Adult forensic mental health service users (*n* = 46) with SMI and meeting the criteria for PTSD will be included in the study. Participants will be randomized after baseline assessment to either treatment as usual plus waiting list for EMDR or to treatment as usual plus EMDR. The EMDR condition comprises nine sessions, around 60 min in length delivered weekly, the first of which is a case conceptualization session. The primary outcomes are clinician and participant-rated symptoms of PTSD, and adverse events. Secondary outcomes include psychotic symptoms, social functioning, level of disability, self-esteem, depressive symptoms, post-trauma cognitions, and broad domains of complex posttraumatic difficulties. A trained assessor blinded to the treatment condition will assess outcomes at baseline, 10 weeks, and 6 months. Additionally, grounded theory qualitative methods will be used to explore participant experience of EMDR for a subset of participants.

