### Randomization, allocation concealment, and blinding

Consenting participants will receive the pre-treatment (T0) measurements. After T0, participants will be randomly assigned to either the EMDR or treatment as usual group. An independent research manager at the District Health Board research office (who is not involved in the study) will generate the random sequence. This allocation sequence will be computer-generated and non-stratified with varying block sizes, which will not be disclosed to the researchers to ensure concealment. After randomization, the research office will notify the trial coordinator from the research team as to the allocation. To ensure allocation concealment, the randomization code will not be released until after the participant has been recruited into the trial, which takes place after all baseline measurements have been completed.

After allocation, the participants will be informed which group they are in. Hence, neither the participants nor the specialized therapists who deliver EMDR will be blinded to the allocation (as it is not practical to undertake blinded EMDR). However, outcome assessors will be blinded to treatment allocation, as will those performing data entry and the trial statistician (MW). Assessors and therapists will emphasize the importance of blinding to the participants and remind them not to reveal the randomized treatment condition. Assessors will avoid contact with the therapists and other caregivers. Assessors will be asked to report any case of unblinding, in which case, another assessor will repeat the entire measurement.

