#### Early completers

We will allow “early completion” when symptoms resolve before the nine sessions are finished. A participant will be considered an early completer of treatment when his or her score on the PTSD Symptoms Scale—Self Report (PSS-SR) is lower than 10 on two consecutive occasions, and if the SUD scores from all situations that are part of the case conceptualization are reduced to zero. If this happens, therapy can be stopped early.

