Health condition(s) or problem(s) studied	PTSD in people receiving care from forensic mental health services
Intervention(s)	EMDR therapy
Key inclusion and exclusion criteria	Inclusion criteria: aged 18–65 years; a lifetime history of a psychotic disorder or a mood disorder with psychotic features as diagnosed according to ICD-10 or DSM-5 criteria; meeting diagnostic criteria for PTSD (Clinician Administered PTSD Scale (CAPS)); current patient of the forensic and rehabilitation mental health services; competent to provide informed consent; likely to remain in the area for the 6-month trial duration (i.e., if a prisoner, release date at least 6 months away; if a patient within a forensic mental health service, their anticipated discharge is at least 6 months away) Exclusion criteria: high suicidality, operationalized as the combination of having a high suicidality score on the Mini International Neuropsychiatric Interview (MINI-plus) or with a suicide attempt within the past 6 months; mental state considered by the treating psychiatrist as too unstable to participate in the trial (participants may be experiencing chronic low-grade symptoms, but cannot be acutely psychotic); insufficient competence in the English language to understand, provide informed consent, and participate in therapy and data collection
Study type	Single-blind, randomized controlled trial
Date of first enrolment	25 May 2018
Target sample size	46
Recruitment status	Currently recruiting
Primary outcome(s)	Change in PTSD symptoms (measured by the CAPS and PSS-SR), treatment safety (measured by the adverse event questionnaire), and acceptability of the EMDR treatment (measured by the TAAS and by qualitative participant feedback)
Key secondary outcomes	Posttraumatic cognitions (PTCI), self-disturbance (TSI-2 Factor 1), posttraumatic stress (TSI-2 Factor 2), externalization (TSI-2 Factor 3), somatization (TSI-2 Factor 4), depression (BDI-II), psychosis (PSYRATS), overall functioning (WHODAS 2.0), social functioning (Social Functioning scale), self-esteem (RSES)

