Secondly, the Posttraumatic Stress Disorder Symptom Scale—Self-Report (PSS-SR) [38] will be administered to assess self-reported severity of PTSD symptoms [39]. The PSS-SR consists of 17 items corresponding to the 17 diagnostic DSM-IV-TR criteria of PTSD which are rated on a 3-point Likert scale, where 0 = *not at all*, 1 = *a little* bit, 2 = *somewhat*, and 3 = *very much*. This yields a total score measuring symptom severity (range 0–51), as well as separate severity scores for re-experiencing (range 0–15), avoidance (range 0–21), and arousal (range 0–15). The PSS-SR will also be administered at T0, T1, and T2, as well as before each treatment session, to assess changes in the PTSD symptoms during treatment. The PSS-SR has revealed satisfactory internal consistency (Cronbach’s α = 0.91), high test–retest reliability (*r* = 0.74), and good concurrent validity (sensitivity = 62%, positive predictive power = 100%, negative predictive power = 82% [38, 40]).

Two primary outcome measures pertain to adverse events. The Adverse Events Questionnaire (AEQ), which we have designed using similar questions to Van den Berg et al. [16], is a checklist that will help establish treatment safety. In 10 questions, the patient is asked to report any experiences they have had over the last 2 months of self-harm, suicide attempt, deliberately hurting another person, excessive use of alcohol, excessive use of drugs, having needed help because of a crisis, moving back to a higher level of security within the services, or any reoffending.

The Adverse Events Session Rating scale will also be used to assess adverse events in the participant before and after treatment sessions (sessions two and three), for example, being suicidal and hearing voices. Participants will respond on a 10-point visual analog scale (from “*no, not at all*” to “*yes, very much*”) to the questions.

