The World Health Organization Disability Assessment Schedule 2.0 (WHODAS 2.0) [47] is a self-report questionnaire that assesses limitations and disability in six domains: cognition; mobility; self-care; getting along with people; life activities, subdivided into household activities and work/school activities; and participation in society. The 12-item version will be used. For each item, respondents rate the level of difficulty experienced, in the prior month, on a 5-point scale from “*none*” to “*extreme or cannot do*”. The WHODAS 2.0 has been found to have good reliability and sensitivity to change across a range of physical and mental health conditions [48].

Psychotic symptoms will be measured by the PSYRATS delusions and hallucinations subscales [49]. The PSYRATS is an instrument that was developed to quantify the severity of delusions and hallucinations. It is commonly used in research studies and clinical settings focussing on people with psychotic illnesses.

Social functioning will be assessed using aspects of the Social Functioning Scale, a measure with sound psychometric properties, established acceptability for patients, and one of the more frequently used social functioning scales in SMI research [50, 51]. It has 79 items covering seven domains of functioning (social engagement/withdrawal; interpersonal communication; pro-social activities; recreation; independence–competence; independence–performance; employment/occupation), with standard scores for each subscale, and an “overall functioning” mean standard score is calculated. For the current trial, a number of questions will be omitted for those residing in secure settings as they are not relevant to that living situation.

Self-esteem will be measured by the Rosenberg Self Esteem Scale (RSES) [52]. This Likert scale has 10 items, each with 4-point scale response options from *strongly disagree* to *strongly agree*. It produces a total ranging from 0 to 30, with scores below 15 considered to reflect low self-esteem. The RSES is likely the most commonly used self-esteem measure in psychology research, and has shown satisfactory validity, reliability, and floor and ceiling effects [53].

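### The blinded-interviewer CAPS and the self-rated PSS-SR are both primary for PTSD efficacy with no order between them, so an efficacy claim could rest on the unblinded scale alone

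*Protocol article*

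**What the plan says.** **Blinding.** The abstract (Methods) states "A trained assessor blinded to the treatment condition will assess outcomes at baseline, 10 weeks, and 6 months", without exempting self-report. The section on randomization, allocation concealment and blinding says that outcome assessors are blinded but that "neither the participants nor the specialized therapists who deliver EMDR will be blinded to the allocation".

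**Primary outcomes.** The abstract announces "The primary outcomes are clinician and participant-rated symptoms of PTSD, and adverse events". The section on primary outcome measurements sets two PTSD measures. The CAPS, a structured interview, is described first. The PSS-SR is second and "will be administered to assess self-reported severity of PTSD symptoms". Table 2 lists them jointly: "Change in PTSD symptoms (measured by the CAPS and PSS-SR".

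**Use of the PSS-SR.** "The PSS-SR will also be administered at T0, T1, and T2, as well as before each treatment session". Only the EMDR arm has sessions before T2; the waiting-list group starts treatment at T2. Under Early completers, one of two conditions for ending therapy early is that the participant's "score on the PTSD Symptoms Scale—Self Report (PSS-SR) is lower than 10 on two consecutive occasions".

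**Testing.** Quantitative data analysis makes all tests two-sided at p < 0.05. It does not rank, combine or adjust for the two PTSD measures. Sample size calculations uses the CAPS alone.

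**The concern.** The control is a waiting list, and its members know they are still waiting. Under those conditions a self-rating can separate the arms through expectation, a wish to please the therapist, or repeated completion in one arm only. Blinding the assessor cannot remove this when the participant is the rater. Nor does the safeguard of having a second assessor repeat a measurement after unblinding.

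Because the PSS-SR is primary alongside the CAPS, a reader following the plan could accept a PSS-SR difference as primary evidence of efficacy when the CAPS shows none. Two problems combine:

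- **Chance:** two routes to success, each at 5%.
- **Bias:** one of those routes is more open to reporting bias. Dividing alpha between the scales would deal with the first problem and leave this one.

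**Working it through.** **1. The plan's own figure.** Inputs from Sample size calculations: CAPS difference 16, SD 16 (d = 1.0), two-sided alpha 0.05, power 0.8, dropout 30%.

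- Normal approximation: n = 2 × (1.960 + 0.842)² / 1.0² = 15.7, so 16 per arm. The exact t test gives 16.7, so 17. The plan states 15, which is close.
- Dropout: 16 / 0.7 = 22.9, so 23 per arm, as stated.

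This calculation involves the CAPS only. I use 16 evaluable (after dropout) and 23 (no dropout) per arm below.

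**2. Who rates, and how often.**

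| | CAPS | PSS-SR |
|---|---|---|
| Status | Primary | Primary |
| Scored by | Blinded interviewer | Participant, aware of arm |
| EMDR arm | T0, T1, T2 | T0, T1, T2 and before each session |
| Waiting list | T0, T1, T2 | T0, T1, T2 |

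With nine sessions the EMDR arm completes the PSS-SR up to 3 + 9 = 12 times (11 if the planning session does not count), against 3 on the waiting list.

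**3. Type I error if either measure suffices, no bias.** Two tests, each two-sided at 0.05, at one visit.

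- Correlation 0: 1 − 0.95² = 0.0975.
- Otherwise: 1 − P(|Z₁| < 1.96 and |Z₂| < 1.96), with Z₁ and Z₂ bivariate normal. Correlation 0.5 gives 0.091; 0.7 gives 0.083.

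The documents give no correlation, so 0 to 0.7 is an assumed range. If the CAPS must be significant first, the error rate returns to 0.05.

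**4. Illustration of reporting bias.** Assume no true effect and a pure reporting shift of d SD on the PSS-SR. The documents give no such figure. For an unadjusted two-sample t test at one visit, the non-centrality parameter is d × √(n/2) with 2n − 2 degrees of freedom. For n = 23 and d = 0.5 it is 0.5 × √11.5 = 1.70, against a critical value of 2.015. Chance of p < 0.05 in favour of EMDR:

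| Assumed shift | 16 per arm | 23 per arm |
|---|---|---|
| 0 | 2.5% | 2.5% |
| 0.2 SD | 7.9% | 9.7% |
| 0.3 SD | 12.7% | 16.7% |
| 0.5 SD | 27.7% | 38.2% |

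If the CAPS were wholly free of bias, at a 0.5 SD shift the PSS-SR would favour EMDR while the CAPS did not in about 27% to 28% of trials with 16 per arm, and 37% to 38% with 23 (normal approximation, correlation 0.3 to 0.7).

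**The case against.** **Disclosure.** The lack of participant blinding is not hidden. The abstract calls the trial single-blind and one primary participant-rated, the blinding section says who knows the allocation, and Table 1 marks each secondary outcome as interview or self-report. This stands. A reader might infer from the abstract sentence that self-ratings are presented as blind; the rest of the document does not support that, and the sentence is merely too broad.

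**No stated success rule.** A reader might also infer that the plan declares the PSS-SR sufficient on its own. It nowhere says so, and an unseen analysis plan might rank the scales. The text leans towards the CAPS: it is described first, is the sole basis of the sample size, and defines the diagnosis. But the choice of primary outcomes is made in this document, jointly and with one significance threshold for all tests. What it fixes leaves the second route open.

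**The CAPS is not immune.** Its blinded interviewer scores answers from participants who know their arm. It removes assessor bias and only part of participant reporting bias. This stands and limits what a CAPS gate can achieve.

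**The bias figures are assumed.** They also use a simple t test, whereas the plan specifies mixed models with baseline covariates. This stands.

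**Early completion adds little.** The rule also requires all distress ratings to reach zero, and it does not change how T1 or T2 is scored. Nothing in the documents gives the direction or size of a repeated-testing effect.

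**Conclusion.** The point holds in a limited form. The protocol makes a blinded-interviewer measure and an unblinded self-rating both primary for PTSD efficacy and sets no order between them. A positive efficacy claim could therefore rest on the measure more open to reporting bias.

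The firmer figure is the two-sided type I error of about 8% to 10% if either measure suffices, which needs only a correlation between 0 and 0.7. The 8% to 38% range for a false PSS-SR result depends on an assumed 0.2 to 0.5 SD shift and does not estimate bias in this trial. The documents do not show that such bias will occur, or that the CAPS is free of it. They support a cheap improvement to the decision rule, not a finding that the design is invalid.

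**What to change.** In the section on primary outcome measurements, in Table 2 and in Quantitative data analysis, state that:

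- the CAPS is the lead, gatekeeping primary for PTSD efficacy;
- the PSS-SR is tested confirmatorily only if the CAPS is significant;
- a PSS-SR difference without a CAPS difference is reported as supportive, unblinded evidence and not as efficacy.

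Two minor wording changes go with this. Limit the assessor-blinding sentence in the abstract to interviewer-rated outcomes. Reconcile the mode of the WHODAS 2.0, which Table 1 marks as an interview while the section on secondary outcome measurements says it "is a self-report questionnaire that assesses limitations and disability in six domains".

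The cost is text only: no new data, visits or participants, and the CAPS-based sample size is unchanged. The sponsor gives up a second route to a positive claim.

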**Discussion:**

This study will contribute to the currently limited evidence base for EMDR for PTSD in forensic settings. It is the first randomized clinical trial to assess the efficacy, risk of harm, and acceptability of EMDR for PTSD in people with SMI in either forensic, mental health inpatient, or custodial settings.

**Trial registration:**

Australia and New Zealand Clinical Trials Network, ACTRN12618000683235. Registered prospectively on 24 April 2018.

## Background

Posttraumatic stress disorder (PTSD) in forensic populations is common, disabling, and often unaddressed [1–7]. There is converging evidence that forensic patients often have extensive trauma histories [8] and that their trauma syndromes, which frequently present with comorbid serious mental illness (SMI), typically schizophrenia spectrum conditions and severe mood disorders [9], in turn can be associated with offending [10].

The symptoms of PTSD include: ongoing re-experiencing of an event or events involving death, or actual or threatened serious injury or violence (e.g., through nightmares or distressing memories); avoiding reminders of the trauma (e.g., places or people associated with it); negative thoughts or feelings pertaining to the trauma (e.g., self-blame or difficulty remembering aspects of what happened); and, finally, physical arousal or reactivity (e.g., startling easily or difficulty sleeping). A formal diagnosis is made when the symptoms are so severe that the sufferer is not able to function adequately in one or more aspects of their life (e.g., at work or in social relationships) [11].

Eye movement desensitization and reprocessing (EMDR) is a talking therapy that was developed for the treatment of posttraumatic states including PTSD [12]. It is now well established as an effective treatment with a strong evidence base [13, 14] and is recommended by the National Institute for Health and Care Excellence (NICE) guidelines and by the World Health Organization for the treatment of PTSD [15]. During EMDR the client is instructed to think about the traumatic event for brief periods while simultaneously tracking the therapist’s fingers (which are moved from side to side) with their eyes. The resulting bilateral brain stimulation is thought to activate the brain’s information processing pathways, enabling more adaptive associations to be made. Over time, this leads to processing of traumatic events into long-term memory. As a result, people become desensitized to the trauma, allowing their symptoms to remit, and their functioning in life to improve [15].

Promisingly, a large randomized controlled trial (RCT) conducted by van den Berg et al. [16] found EMDR of significant benefit in community patients with serious mental illness and PTSD, showing improvement in both posttraumatic stress symptoms and the symptoms of comorbid mental illnesses, including psychotic disorders. Adverse events and rates of re-victimization were lower in the EMDR group than in the control group.

Despite strong evidence for high rates of PTSD in forensic populations [1], there are no trials testing EMDR compared with a control group in the forensic setting. There are, however, favorable case reports of EMDR being used in forensic settings, with at least six case studies demonstrating reductions in offence-related PTSD symptoms [17–22].

Untreated PTSD in forensic services has costs to the individual, their families, and society; costs which may be exacerbated where PTSD presents concurrently with other serious SMI. PTSD may serve as a chronic stressor, worsening symptoms of other mental conditions, and/or predisposing people to substance misuse, further compromising their recovery.

EMDR has the potential to be of benefit to the forensic mental health population. The intervention is particularly suited to people in secure care because it can take place anywhere, and for people with SMI because it does not require homework. The desensitization in EMDR is limited to imaginal activities and does not involve the real-world (in vivo) graduated exposure to trauma triggers generally required in other evidence-based PTSD therapies.

This trial builds on the work of van den Berg et al.’s positive findings in RCTs examining EMDR for PSTD in people with psychotic illnesses [23–25], extending this to samples in forensic inpatient, outpatient, and prison services who have the additional complex overlay of criminal offending issues.

## Study aims

### Primary aim

In a sample of people receiving forensic and rehabilitation mental health care, we aim to examine: the efficacy of EMDR versus the waiting list for treating PTSD symptomology; and the safety and acceptability of EMDR versus the waiting list as indicated by adverse events.

### Secondary aims

Other aims are to assess the impact of EMDR versus the waiting list on psychotic symptoms, social functioning, self-esteem, and depressive symptoms. Additionally, this study aims to gain in-depth insight into the subjective experience of EMDR for consumers of forensic mental health services.

**Fig. 1 Fig1:**
[figure not shown]
Consolidated Standards of Reporting Trials (CONSORT) flow diagram. AEQ, Adverse Events Questionnaire; BDI-II, Beck Depression Inventory—second edition; CAPS, Clinician Administered PTSD Scale; EMDR, eye movement desensitization and reprocessing; MINI, Mini International Neuropsychiatric Interview; PSS-SR, Posttraumatic Stress Disorder Symptom Scale—Self-Report; PSYRATS, Psychotic Symptom Rating Scales; PTCI, Posttraumatic Cognitions Inventory; RSES, Rosenberg Self-Esteem Scale; SFS, Social Functioning Scale; TAAS, Treatment Acceptability/Adherence Scale; TSI-2, Trauma Symptom Inventory—second edition; TSQ, Traumatic Symptom Questionnaire; WHODAS, World Health Organization Disability Assessment Scale

